### Dropout and missing data management

Given the longitudinal design of the study, particular attention will be paid to participant retention and data completeness. Protocol completion will be defined as participation in at least 80% of the scheduled sessions (i.e., at least 8 of 10 sessions).

The primary analysis will follow the intention-to-treat (ITT) principle, including all randomized participants with available outcome data in the analysis set. Linear mixed-effects models will use all available repeated-measures data under the missing-at-random assumption, without formal imputation. The extent and patterns of missing data will be reported descriptively.

An additional per-protocol analysis will be conducted, including only participants who meet the predefined completion threshold.

Dropout rates, reasons for withdrawal, and patterns of missing data will be reported descriptively to support transparent interpretation of the study findings.

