**Methods:**

A prospective, phased, randomized waitlist-controlled intervention study will include adults aged 18–70 years who have experienced a stroke at least 3 months before enrollment. The first recruitment phase will be conducted in a single outpatient neurological rehabilitation center in the Community of Madrid, Spain, with subsequent recruitment phases planned at additional outpatient neurological rehabilitation centers within the Community of Madrid until the required sample size is achieved. Two groups will be formed: an experimental group receiving standard rehabilitation care plus a structured music-based intervention consisting of 10 sessions and a waitlist group receiving only standard rehabilitation care during this period, followed by the structured music-based intervention. Assessments will be carried out at week 0 (baseline), week 5 (post-intervention), and week 10 (after group crossover), with an additional follow-up at 3 months. The primary outcome will be motor function. Upper-limb motor function will be assessed as a secondary motor outcome, while executive functioning and stroke-specific quality of life will be examined as exploratory outcomes. Analyses will follow the intention-to-treat principle, with additional analyses conducted for participants completing at least 80% of sessions. A linear mixed-effects model will be used to estimate the main effect of the intervention on the primary motor outcome, with additional secondary and exploratory models performed for upper-limb motor function, executive functioning, and stroke-specific quality of life. The model will include time, group, and the interaction between group and time as fixed effects, with time since stroke included as a covariate. Additional analyses will be conducted using intraclass correlation coefficients to explore the agreement between participant and family member reports of executive function.

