### Study design

This is a prospective, phased, randomized waitlist-controlled intervention study with a parallel-group design, aimed primarily at evaluating the effects of the intervention on motor function. Upper-limb motor function will be assessed as a secondary motor outcome, while executive functioning and stroke-specific quality of life will be examined as exploratory outcomes. Participants will be randomly allocated to either an experimental group or a control/waitlist group.

The study will be implemented in successive recruitment phases. The first phase will be conducted in a single outpatient neurological rehabilitation center in the Community of Madrid, Spain, and subsequent phases will extend recruitment to additional outpatient neurological rehabilitation centers within the Community of Madrid until the required total sample size is achieved.

In the first recruitment phase, approximately 24 participants are expected to be included, with 12 participants allocated to each group. Recruitment will then continue in subsequent phases across additional centers, maintaining the same eligibility criteria, intervention protocol, assessment schedule, randomization procedures, and outcome measures, until the planned sample of 76 participants is reached.

Two groups will undergo the same overall rehabilitation process. Over a total of 5 weeks (two sessions per week), the experimental group will receive their standard rehabilitation care complemented by a program of music-based activities. The control/waitlist group will receive only standard rehabilitation care during the first 5-week intervention period and will subsequently undergo the music-based program after the experimental group has completed it, thereby effectively switching their roles.

This design ensures that all participants benefit from the intervention while allowing temporal comparison between the groups. This structure is consistent with previous studies of similar music-based rehabilitation programs and supports ethical rigor by ensuring that all participants receive a potentially beneficial intervention.

All participants will be assessed at baseline (week 0), after 5 weeks (post-intervention), and again at 10 weeks (after crossover). A 3-month follow-up will be conducted to explore the maintenance of potential effects.

The study has been preregistered in OSF Registries.^1^ This record is reported as an open science preregistration and is not presented as a clinical trial registry.

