Musical parameters, including tempo, rhythmic complexity, movement amplitude, instrument type, and level of facilitator cueing, will be adapted according to participants’ motor capacity, fatigue, comprehension, and emotional response. Tasks will begin at a level that allows successful participation and will progress by increasing rhythmic complexity, tempo, task duration, bilateral involvement, range of movement, memory load, or degree of independence. Task difficulty will be reduced if participants show excessive fatigue, frustration, loss of postural control, inability to follow instructions, or emotional discomfort. Treatment fidelity will be supported through facilitator training, use of the standardized session protocol, and completion of a session checklist documenting attendance, activities delivered, adaptations made, participant engagement, adverse events, and deviations from the protocol.

Session checklists will be reviewed periodically by the research team to monitor adherence to the protocol and identify deviations requiring corrective action.

The intervention consists of a 10-session structured program delivered twice per week over 5 weeks, including 6 individual sessions and 4 group-based sessions.Individual sessions (30–40 min): Focused on evaluation and individualized work on motor engagement, rhythmic participation, and emotional regulation.Group sessions (45 min): Conducted collectively with all participants, focused on social interaction, motor coordination, and emotional support.

These group-based and receptive components are informed by music therapy and music-based rehabilitation approaches commonly used to support emotional regulation, social interaction, and quality of life in rehabilitation populations. Group singing, shared rhythmic activities, and guided listening are consistent with rehabilitation-oriented music-based frameworks that emphasize emotional expression, social engagement, and patient-centered rehabilitation (6, 7).

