### Assessment

Assessments will be conducted at three main time points, plus one follow-up:Baseline (week 0): Prior to the start of the program. Includes assessment of motor, cognitive, and quality-of-life domains.Week 5 (post-intervention for the experimental group): Repetition of all measures to evaluate initial changes in the experimental group compared to the waitlist group.Week 10 (after the waitlist group intervention): Comprehensive evaluation of both groups following completion of the intervention.Three-month follow-up: Additional evaluation to explore maintenance of potential effects, including quality of life and daily functioning.

Standardized instruments will be used at all time points to measure motor, cognitive, and quality-of-life outcomes. In addition, participants’ perspectives on acceptability and perceived usefulness will be explored qualitatively during the 3-month follow-up interview, in line with multidomain rehabilitation research (12, 30). When feasible, caregivers or family members will also be invited to provide complementary perspectives on functional changes and everyday impact.

Outcome assessments will be conducted by professionals with a clinical background in neuropsychology or rehabilitation. All assessors will receive standardized training in the administration and scoring of the study measures before participant recruitment to ensure consistency and reliability of data collection.

Standard Protocol Items: Recommendations for Interventional Trials (SPIRIT) schedule of enrollment, interventions, and assessments (Table 2).

**Table 2 tab2:** Standard Protocol Items: Recommendations for Interventional Trials (SPIRIT) schedule of enrollment, interventions, and assessments.

Activity	-t1	Baseline (week 0)	Mid-intervention (week 3)	Post-phase 1 (week 5)	Post-crossover (week 10)	Follow-up (3 months)
Eligibility screening	X					
Informed consent		X				
Randomization		X				
Structured music-based intervention: experimental group		X	X	X		
Structured music-based intervention: control/waitlist group				X	X	
Adherence		X	X	X	X	
Assessment: FMA, Action Research Arm Test (ARAT), and WCST		X		X	X	X
Assessment: Behavior Rating Inventory of Executive Function–Adult Version (BRIEF-A)		X		X	X	X
Assessment: Stroke-Specific Quality of Life Scale (SS-QOL)		X		X	X	X
Adverse event reporting		X	X	X	X	X

X indicates that the corresponding activity, intervention, assessment, or reporting item takes place at that time point.

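### The 8-of-10-session per-protocol rule does not fit the week-5 comparison: waitlist participants can meet it only after that outcome is measured, so the estimate is open to selection bias of unknown size and direction

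*Protocol article*

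**What the plan says.** Under Dropout and missing data management, the protocol article states: "Protocol completion will be defined as participation in at least 80% of the scheduled sessions", spelled out there as 8 of 10. It then adds: "An additional per-protocol analysis will be conducted, including only participants who meet the predefined completion threshold". The Methods paragraph of the abstract gives the same rule without distinguishing the arms: "with additional analyses conducted for participants completing at least 80% of sessions".

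The sessions counted are those of the music programme (Music-based intervention): "The intervention consists of a 10-session structured program delivered twice per week over 5 weeks, including 6 individual sessions and 4 group-based sessions".

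Study design fixes when each arm can attend them: "The control/waitlist group will receive only standard rehabilitation care during the first 5-week intervention period". The waitlist arm takes the programme afterwards. The Assessment section places the between-arm comparison at week 5: "Repetition of all measures to evaluate initial changes in the experimental group compared to the waitlist group". The next assessment falls after the waitlist arm has been treated: "Week 10 (after the waitlist group intervention): Comprehensive evaluation of both groups following completion of the intervention".

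The primary analysis follows intention to treat and does not use the threshold. The mixed model described under Statistical analysis adds one covariate, time since stroke.

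**The concern.** A completer analysis has to be defined on what participants did during the period being compared. Here the threshold counts music sessions, and one arm is offered none in that period. Membership of the per-protocol set therefore means different things in the two arms at week 5.

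The Introduction itself gives a reason why this could matter. It says that depression and anxiety lower adherence to treatment and that emotional disturbance can worsen recovery. The same factor could therefore affect both attendance and motor change, and adjusting for time since stroke does not address it. In the waitlist arm there is a further route: a participant's state at week 5 may influence whether they go on to attend the sessions that decide their inclusion.

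At stake is whether the per-protocol figure says anything reliable about the effect of taking the programme. The primary result is not at stake.

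**Working it through.** **Threshold.** 80% of 10 sessions = 0.80 x 10 = 8, which reproduces the protocol's figure.

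**Timing.**

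| | Experimental | Waitlist |
|---|---|---|
| Music sessions possible before week 5 | 10 | 0 |
| Period that decides inclusion | weeks 0-5 | weeks 5-10 |
| Inclusion relative to the week-5 outcome | settled by then | decided wholly afterwards |

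No waitlist participant can meet the threshold by week 5. Two readings of the rule remain.

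- *Both arms filtered (the literal reading).* A waitlist participant who leaves just after week 5 with complete control-period data is dropped. An experimental participant who attended 8 sessions and leaves at the same moment is kept.
- *Experimental arm only.* Its completers are compared with all controls, so the filter breaks the randomised comparison on one side.

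**How large could the distortion be?** The documents give no completion rate and no link between completion and outcome, so both are assumed here. Let p be the completion rate and r the correlation between a latent tendency to complete and week-5 change. Use SD = 12 from the Sample size section and a true effect of 0. The mean change among completers then exceeds the arm mean by

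r x SD x phi(z_p) / p,

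where phi is the standard normal density and z_p the normal quantile of p. For p = 0.80 and r = 0.3: 0.3 x 12 x 0.280 / 0.80 = 1.26 points.

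A simulation with 1,000,000 per arm, p = 70% to 90% and r = 0.1 to 0.5 gave these spurious differences in Fugl-Meyer points:

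| Selection | Range | p = 80%, r = 0.3 |
|---|---|---|
| Experimental arm only | +0.2 to +3.0 | +1.3 |
| Both arms, opposite direction in waitlist | +0.5 to +6.0 | +2.5 |
| Both arms, same r, waitlist completion 10 percentage points lower | -0.2 to -0.9 | -0.5 |
| Both arms, same p and r | about 0 | about 0 |

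For scale, the planning difference in the Sample size section is 4 points.

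**Precision of the alternative.** Take 38 per arm and SD 12 as the protocol gives them, assume 80% completion, and ignore loss before week 5.

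- Intention-to-treat difference: SE = 12 x sqrt(2/38) = 2.75.
- Complier-type estimate: 2.75 / 0.80 = 3.44. With session count as exposure, scaled to ten sessions, the same value follows if mean attendance is 8 of 10.
- Naive comparison, both arms filtered: 38 x 0.80 = 30.4, about 30 per arm, so SE = 12 x sqrt(2/30) = 3.10.
- Naive comparison, experimental arm only filtered: 12 x sqrt(1/30 + 1/38) = 2.93.

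**Effect of a binary 8-session exposure.** Suppose 80% complete and gain 4 points, while 20% attend partially and gain b points. The estimate is (0.8 x 4 + 0.2 x b) / 0.8 = 4 + 0.25b. For b = 2 to 4 it is 0.5 to 1.0 points too high. A complier estimate built on that cut alone is therefore not a clean remedy.

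**The case against.** The strongest reply is that every participant is offered the same ten sessions. Filtering both arms on completion when offered then compares people who complete once offered, a rough version of the group a complier analysis targets. If neither the five-week delay nor the week-5 state changed who completes, the comparison would be fair, as the last row of the simulation shows. This stands as a reason not to call bias certain. It does not rescue the rule, because nothing in the protocol secures that condition.

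A second reply is that operation by arm and time point is commonly left to an analysis plan, which is not shown. That stands in part. But the article does more than leave detail open: it states one threshold for all participants, and that threshold cannot be met by one arm in the period compared.

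A reader might infer that the estimate is biased upwards, since completers are likely to be fitter and more motivated. The documents do not support a direction: same-direction selection with lower waitlist completion gave negative values. A reader might also expect the result to be offered as support for the primary finding. The article calls it only an additional analysis.

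**Conclusion.** The concern holds in this form: the per-protocol rule does not fit the week-5 comparison on either reading, and the resulting estimate is open to selection bias of unknown size and direction. For the waitlist arm, the selecting behaviour lies wholly after the outcome.

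The simulated range of about -0.9 to +6.0 points rests on assumed completion rates, correlations and selection patterns. It shows that the distortion could be material against a 4-point planning difference, not that it will be. A single bias figure would need a choice between the two readings and a completion rate, and the documents supply neither.

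The intention-to-treat analysis is untouched. The point should be corrected, but it does not threaten the trial's main conclusion.

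**What to change.** For the week-5 contrast, replace the completer filter with a complier-type (instrumental-variable) estimate:

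- keep all randomised participants with week-5 data in their randomised arm;
- use randomised arm as the instrument;
- use the number of music sessions attended by week 5 as the exposure, zero for the waitlist arm;
- state the assumption that assignment acts on the week-5 outcome only through sessions attended;
- use the 8-of-10 cut only as a sensitivity analysis, stating that it assumes no effect of partial attendance.

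If a per-protocol set is kept, define it separately for each arm using only information up to week 5, and label the comparison as non-randomised. Use waitlist completion in weeks 5-10 only for descriptive or within-group analyses.

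The cost is one paragraph of text and a somewhat wider interval, as shown in the precision check. Session attendance is already to be recorded, and the Study status section says recruitment has not started, so the change can be made before any data exist.

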## Discussion

While previous studies have reported benefits of music-based interventions, neurologic music therapy, and music-supported interventions in stroke rehabilitation, the majority of interventions have focused on isolated domains rather than adopting a multidimensional approach (8, 9, 21). Although contemporary rehabilitation frameworks emphasize the importance of integrating motor, cognitive, and psychosocial aspects of recovery (4, 5, 15), these domains are still often addressed separately in clinical practice, which may limit the overall effectiveness of rehabilitation programs.

Given the relatively brief duration of the intervention, the study is primarily powered and conceptually oriented toward motor outcomes. Executive functioning and stroke-specific quality of life are included as exploratory outcomes, as changes in these domains may require longer or more intensive interventions and may be influenced by multiple contextual and rehabilitation-related factors.

Therefore, the findings related to executive functioning and stroke-specific quality of life will be interpreted as preliminary signals of potential broader effects rather than as confirmatory evidence of efficacy.

In particular, any observed changes in executive functioning or quality of life should be interpreted in relation to participants’ baseline impairment, concurrent rehabilitation exposure, emotional status, and social participation, rather than attributed solely to the music-based intervention.

The added value of this protocol lies not only in the structural organization of sessions but also in the integration of motor rehabilitation activities with exploratory executive and quality-of-life-related components within a single coherent intervention. While conventional post-stroke rehabilitation and many music-based interventions tend to address these domains separately or sequentially, this protocol is designed to address these domains within the same structured rehabilitation-oriented context. By combining rhythmic motor training, cognitively demanding musical tasks, and group-based activities aimed at emotional and social engagement, the program reflects the complex and interdependent nature of post-stroke recovery and aims to enhance the ecological validity and functional relevance of rehabilitation.

The main strength of this study lies in its integrative approach, delivered in a real-world outpatient rehabilitation setting. The use of standardized and validated outcome measures across domains will provide relevant data to inform future research and rehabilitation practice.

Nonetheless, the study’s primary aim is to evaluate the effects of the intervention on motor outcomes and to provide preliminary information on its potential role in post-stroke rehabilitation. Although this study is powered to detect clinically significant differences in motor outcomes, it should be interpreted as an initial evaluation of an integrative intervention model.

If the intervention demonstrates favorable results, it could be incorporated as a complementary strategy within multidisciplinary post-stroke rehabilitation programs. Future research should aim to replicate these findings in larger and multicenter studies.

### Limitations

This randomized waitlist-controlled intervention study presents several inherent limitations. First, outcome assessors will not be blinded, which may introduce measurement bias despite the use of standardized procedures and trained personnel. Second, although this study begins in a single outpatient rehabilitation center, recruitment is planned to proceed in successive phases across additional centers in the Community of Madrid. This phased recruitment strategy may improve feasibility but may also introduce some variability between centers, which will be addressed through standardized intervention procedures, assessor training, fidelity monitoring, and statistical adjustment when appropriate. Third, the relatively short duration of the intervention may reduce the magnitude of observable effects.

In addition, although the sample size was determined through an *a priori* calculation, potential dropout, variability in clinical profiles, and differences in recruitment flow across centers may still affect statistical power and study implementation. These factors should be considered when interpreting the findings. Future studies may explore longer or more intensive protocols and broader multicenter recruitment strategies to further evaluate the impact of integrative music-based interventions.

### Study status

Recruitment has not yet started. The first recruitment phase is planned to begin in a single outpatient neurological rehabilitation center in the Community of Madrid, with subsequent phases extending to additional centers until the required total sample size is achieved. Recruitment is expected to be completed within approximately 1 year. The study has been preregistered in OSF Registries. The protocol version is 1.0 (2 March 2026).

### SPIRIT guidelines

This protocol has been structured using the Standard Protocol Items: Recommendations for Interventional Trials (SPIRIT) statement as a reporting framework to ensure transparency and methodological quality. The schedule of enrollment, interventions, and assessments is presented in Table 2 following SPIRIT recommendations. The SPIRIT checklist is provided in the Supplementary material, following the SPIRIT 2025 statement (37).

In addition, the checklist itself has been completed and included in Supplementary material 2, with page references for each SPIRIT item.
